### Intervention process measures

For participants of the MME intervention, we use a fidelity checklist to monitor that the core components of each session are implemented and track any deviations. This is confirmed during weekly supervision meetings. We also track attendance to ascertain the dosage of MME for each participant. At baseline, we qualitatively ask participants what they hope to gain from the intervention, and at completion, we ask them both what they gained and any changes they would recommend for the future. Because one of the primary goals of the intervention is building social support, at 16-week follow-up we also qualitatively ask the participants if they have stayed in continued contact with their fellow group members, the group leaders, and/or any other counselors or support groups.

### Data management

As part of capacity building, the data center is located at the University of Botswana. All data is collected and entered by trained research staff to be stored virtually on the University of Pennsylvania (UPenn) instance of REDCap. All assessments are recorded on the final version of the case reporting forms (CRFs) and inputted into the secure web-based data management system operated by the Data Management Unit (DMU) of the University of Botswana.

During data collection, security of the web-based data entry system is maintained through the use of a double authentication system. Each system user is assigned two username/password combinations. The first username/password combination is one selected by the registered user and provides access to the main data management website. Access to the website is limited to authorized users by the following condition: (1) all users must become registered with the DMU and (2) access to the DMU website will be restricted to study personnel who work with the UPenn instance of REDCAP and must be approved by the Director of DMU. The second username and password are assigned by the DMU and provides access to the data entry portion of the website. Strict standards are enforced when providing access to the data entry system. A co-investigator validates users in writing for access and security assignment. Additionally, all users of the web data entry system are required to complete CITI training and certification. The data center is unblinded and will adhere to the Data Safety and Monitoring Plan (DSMP), which informs reports, database locking, and analysis. A Data Safety and Monitoring Board (DSMB) will meet every 6 months to monitor adverse events (AEs) and safety outcomes. The DSMB consists of 3 experienced, doctoral-level HIV researchers (> 5 years of research in the field) who will meet every 6 months to review any adverse events and safety outcomes, and independently determine whether study activities will (1) continue as planned or (2) stop pending full IRB review and only continue pending subsequent IRB approval. Study personnel will abide by the determination of the DSMB.

In regard to adverse events, we anticipate two events that may occur, intimate partner violence, and depression and suicidal ideation. In order to protect the privacy of participants and to mitigate the possibility of intimate partner violence, protections for participant privacy will include the following: contact only with the participant; no study-related information will be left on answering machines or other devices; no study-related information will be left with individuals who reside within the household. These procedures will also be followed when participants are contacted about the longitudinal evaluation at 16-week follow-up. When an instance of intimate partner violence is disclosed either during an anti-stigma group session or during the baseline or follow-up evaluation, the study team member who identified the event will report the date, description of the event, duration, severity, measures used to ameliorate effects of the event, and type of referral. The Project Director (AHO) will be notified immediately, and the report form will be reviewed and signed by the PIs (LHY and MB) within 24 h who will be responsible for ensuring that appropriate actions have been taken. The participant will be immediately referred to psychiatric counseling by a clinician under the supervision of our expert in-country psychiatrist Consultant (PO) and other supportive services (e.g., domestic violence support group). The clinician will conduct an in-person clinical evaluation within 24 h, and if the participant is found to be experiencing significant psychiatric distress, this clinician will immediately connect the participant with clinical services in the Princess Marina Hospital Department of Psychiatry, which will address any distress via in-person outpatient meetings and continuing therapy sessions as needed.

Study participants may disclose depression and suicidal ideation via the following methods: (1) during the anti-stigma intervention group sessions and (2) via the CES-D (see “primary outcomes”) measure at baseline and at 16-week follow-up (i.e., if any participant scores > 16 on the CES-D, the cut-off indicating probably clinical depression). If either of these conditions take place, then the procedures for intimate partner violence as described above will be initiated, including notifying the Project Director and PIs and the conducting of a clinical evaluation, within 24 h. If needed, the participant will be connected with a treating clinician in the Princess Marina Hospital Department of Psychiatry and provided with continuing therapy sessions as needed. The evaluating clinician will determine based upon his/her clinical evaluation whether the depression and/or suicidal ideation reaches a magnitude that necessitates removal from study participation. If removal from the study takes place, that participant will no longer attend stigma intervention sessions or participate in the follow-up evaluation; they will also be given the option to remove their data from the study. Regarding reporting of adverse events in trial publications, within the papers a separate section will restate how we report/record adverse events, a brief description of said events, and then how the study team addressed them.

Data analysis will be conducted by the biostatistician (MG). As part of an annual data audit, a clinical research compliance assessment will take place within 90 days of the IRB approval expiration date to assess the prior year’s activity. This is done by the UPenn in-country regulatory staff that are independent from the study team. This audit uses UPenn compliance tools that include a plan for reassessment if there are any issues that need to be addressed; the Research Director for the Botswana-UPenn Partnership will sign off on this process. The results are shared with the study team and all documentation will be completed by the Principal Investigator (LHY) and study staff. In addition, and in regard to data completeness and quality, we are conducting preliminary analyses in order to examine the data in real time and also utilize REDCap data completeness checks. The Principal Investigator (LHY) will also have access to these analyses. Should the trial need to be terminated, the Principal Investigator is responsible to make the final decision to terminate the trial.

All hard copy data are kept in locked filing cabinets in a locked office at all times. All data, including viral load and CD4 counts, are kept according to study participant number (de-identified). De-identified data including all paper interviews are kept separate from confidential data, such as contact information. Data is entered at University of Botswana situated offices and is subsequently stored at the Botswana-UPenn office. All data, once returned to the BUP study offices, are not be permitted to be removed. After data cleaning and analysis activities have concluded, all identifiable data, including patient locator forms, will be destroyed.

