This pilot study of MME collaborates with health clinics offering antenatal services under the Greater Gaborone District Health Management Team (GGDHMT) to conduct a pragmatic clinical trial [68, 69] of an innovative, culturally tailored stigma reduction intervention among pregnant mothers diagnosed with HIV. The intervention builds on prior evidence-based strategies while also integrating WMM for pregnant mothers in Botswana (see “Intervention rationale and components”). We named our intervention “MME” (pronounced “mm-eh”), short for “Mothers Moving towards Empowerment.” *Mme* is also a Setswana term used to address a respected woman. We utilize a pragmatic study design that retains all core elements except for randomization, which was not feasible among this complex population where we must group together women who are at approximately the same stage of pregnancy at the same time. Instead, we use systematic assignment by the experimenter to MME or a control group receiving treatment as usual (TAU). We measure primary and secondary outcomes at three time points (pre-intervention, immediately post-intervention, and at 16-week follow-up postpartum). All details regarding the protocol sections can be located through the SPIRIT checklist (Additional file 1).

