Participants are reimbursed for transportation costs for MME sessions and assessments at baseline, post-MME (intervention group only), and 16-week postpartum (approximately week 56 after calculated date of conception). Since MME is an optional stigma reduction to complement on-going clinical care, it does not entail ancillary or post-trial care.

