### Comparator: treatment as usual

Control participants receive TAU, including using free ART and antenatal services as they wish. Budget constraints do not allow us to implement a time and attention placebo control condition; this threat to validity in this pilot study will be accounted for in a future RCT. Control condition participants are assessed on all primary outcomes at the same time points as the intervention group (Fig. 2), except for immediately following intervention.

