### Assessments and outcome measures

All assessments are enumerated in Table 1, including their domain (name of the outcome), specific measurement, metric, method of aggregation, and time points. The three main time points are (1) baseline (< 28 weeks gestational age), post-intervention (immediately following completion of 8-session intervention, intervention group only), and follow-up (16 weeks postpartum). Primary outcomes for the mother include HIV stigma, psychosocial outcomes, treatment adherence, and HIV outcomes (e.g., viral load). Secondary outcomes for the infant include birth outcomes and early infant health. Stigma and psychosocial outcomes are collected via self-report questionnaires; all other outcomes are collected via health/medical records for the mother and infant. In addition, there are no additional studies using participants’ data and there are also no biological specimens that will be collected. If there are other studies to be conducted, there will be a separate procedure for additional consent.

**Table 1 Tab1:** Overview of measures

Assessment measure	Baseline (< 28 weeks gestational age)	Post-MME	Follow-up (16 weeks postpartum)	Comparison metric

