**Psychosocial outcomes**				
Quality of life (PROMIS-8)	ALL	MME	ALL	1,2,3,4,5
Depressive symptoms (CES-D)	ALL	MME	ALL	1,2,3,4,5
Post-traumatic stress symptoms (PCL-5)	ALL	MME	ALL	1,2,3,4,5
Social functioning (WHODAS-12)	ALL	MME	ALL	1,2,3,4,5
Social support (6 items)	ALL	MME	ALL	1,2,3,4,5

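### The CES-D safety trigger leaves out the post-MME assessment, so a score above 16 on that occasion starts no 24-hour evaluation as the rule is written

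*Protocol article*

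**What the plan says.** The adverse-event text in the protocol article (Data management) names depression and suicidal ideation as one of two anticipated adverse events and gives two routes by which they may come to light. The first is disclosure during the intervention group sessions. The second is the CES-D "measure at baseline and at 16-week follow-up (i.e., if any participant scores > 16 on the CES-D", a score the article describes as its cut-off for probable depression. The consequence is then stated: "If either of these conditions take place, then the procedures for intimate partner violence as described above will be initiated". Those procedures include telling the Project Director and the principal investigators and carrying out a clinical evaluation, within 24 h, with linkage to hospital psychiatry if needed.

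The assessment schedule has one more occasion. In Table 1 the row "Depressive symptoms (CES-D" is marked for all participants at baseline, for MME participants post-MME, and for all participants at 16 weeks postpartum. Four other places treat the post-MME assessment as a separate study visit:

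- Introduction, last paragraph: outcomes are measured "at three time points (pre-intervention, immediately post-intervention, and at 16-week follow-up postpartum".
- Recruitment: transport is reimbursed for "assessments at baseline, post-MME (intervention group only), and 16-week postpartum".
- Comparator: controls are assessed "at the same time points as the intervention group (Fig. 2), except for immediately following intervention".
- Assessments and outcome measures: the occasion is "post-intervention (immediately following completion of 8-session intervention, intervention group only".

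**The concern.** The safety rule and the schedule do not match. The trial collects a depression screen from every intervention woman while she is still pregnant, yet the rule that turns a high score into action names only the other two occasions.

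This concerns patient safety, not the efficacy analysis or power. The group sessions, co-led by a mental health clinician, are a named route while they run. The post-MME form is completed once they have finished, so they cannot act on that score. The next named trigger is the 16-week postpartum visit, after late pregnancy, delivery and the early postpartum months.

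**Working it through.** No published figure needs reproducing. The check sets the trigger list against the schedule and then counts forms.

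**Occasions compared**

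| CES-D occasion | Scheduled for (Table 1) | Named as a trigger (Data management) |
|---|---|---|
| Baseline | all | yes |
| Post-MME | MME only | no |
| 16 weeks postpartum | all | yes |

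**Could the text still cover post-MME?**

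1. *Through the group-session route.* No. The assessment is defined as following completion of the eight sessions, and the route concerns disclosure in a session, not a questionnaire score.
2. *Through the word follow-up.* No. The trigger specifies the 16-week follow-up, and the assessment section lists post-intervention separately from follow-up.
3. *Through the reference to any participant.* No. That phrase explains the CES-D at the two named occasions. It widens who is covered, not when.
4. *Through another section.* None extends the CES-D trigger to post-MME.

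**Share of forms not covered**

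- Per MME woman: 3 scheduled, 2 named, so 3 − 2 = 1 not named.
- Per TAU woman: 2 scheduled, 2 named, so 0 not named.
- Per block of 3 MME and 1 TAU (planned 3:1 ratio): scheduled 3 × 3 + 1 × 2 = 11; not named 3 × 1 = 3; 3/11 = 27.3%.
- Example sample of 15 and 5 (Sample size and power): scheduled 15 × 3 + 5 × 2 = 55; not named 15; 15/55 = 27.3%.
- Example total of 40, with an assumed split of 30 and 10: scheduled 30 × 3 + 10 × 2 = 110; not named 30; 30/110 = 27.3%.

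The ratio alone fixes the percentage; the sample size changes only the count. All counts assume that every scheduled form is completed.

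**Time to the next named trigger**

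Sessions are to finish before week 36 (Eligibility; Condition assignment and blinding), and the postpartum visit falls at about week 56 (Recruitment). For a term delivery, and treating both week counts as on the same clock, 56 − 36 = 20. A woman whose sessions end close to week 36 would wait about 20 weeks. The wait is longer if her sessions end earlier and shorter if she delivers preterm.

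**The case against.** The mismatch itself is hard to dispute. The case on the other side concerns how to read it and how much it weighs.

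- **The exclusion is inferred.** The text opens descriptively and never says that a post-MME score is to be ignored. That is fair as to intent, and an oversight is the likelier explanation. But the procedure is tied to either of two stated conditions, and this score satisfies neither.
- **The article's safety lists may not be exhaustive.** Intervention rationale and components refers any participant who discloses abuse to study personnel for counseling, without limiting the time point, although the adverse-event text lists specific occasions for intimate partner violence. It also gives MME participants contact details for psychological services. This softens the parallel gap for partner violence, where only the reporting and 24-hour steps are unnamed at post-MME. It does not cover a CES-D score.
- **An unseen document may close the gap.** The data center "will adhere to the Data Safety and Monitoring Plan (DSMP), which informs reports, database locking, and analysis", and that plan is not shown. It may hold a fuller rule, so whether staff would in practice fail to act cannot be known. The article's explicit list would still contradict its own schedule.
- **The 27% is a count of forms, not a risk.** This stands. The women who could be missed are those above 16 post-MME who disclosed nothing in a session. Some will already have been evaluated after a high baseline score, and all are due to be screened again at 16 weeks.

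**Conclusion.** The concern holds. Followed exactly, the rule takes no action on a post-MME score above 16, which is one of three scheduled CES-D forms for each MME woman and 3 of 11 (27%) across the trial at 3:1 with complete forms. How many women this would affect cannot be estimated from the article.

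Confidence is high that the stated rule and the schedule conflict. The practical consequence is less certain, because it depends on staff behavior and on a monitoring plan that is not shown. A written safety rule should not rely on staff going beyond it. The correction should be made, although nothing here suggests a deliberate choice to withhold care.

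**What to change.** In Data management, replace the two named CES-D occasions with any study assessment, and name post-MME explicitly. For consistency, add the post-MME assessment to the occasions listed there for disclosure of intimate partner violence, so that the reporting and 24-hour steps apply then too. If the Data Safety and Monitoring Plan lists trigger occasions, check that it agrees. The clinical content of the procedure need not change.

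The cost is a short amendment, a note to staff and possibly a few more evaluations within 24 h. No assessments are added. One side effect should be tracked: only MME women have this extra screen, and the evaluating clinician may refer a woman for therapy or remove her from the study, which ends her follow-up. Triggered evaluations, referrals and removals should therefore be recorded by arm and occasion, so that any influence on the 16-week comparison is visible.

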### Statistical analysis

We will examine baseline demographic characteristics of the intervention and control group and statistically test for differences between the groups on key characteristics to characterize the samples. Given the relative small sample size, nonparametric tests will be used to examine differences between groups. We will use bivariate analysis to compare primary outcomes of the mother’s reduced self-stigma, psychosocial outcomes, and treatment adherence, and secondary outcomes for infants including birthweight, timing of delivery, and developmental milestone between the treatment and control group using an intent-to-treat analysis at baseline and 4-month follow-up. Regarding missing data, we will conduct analyses based on complete data on each outcome and we will remove anyone if they do not have complete data for the outcome being assessed. Sensitivity analyses will be conducted based on the dose of intervention received using several different cut-points: (1) attended at least one session (yes/no), (2) number of sessions attended (count), (3) attended five or more sessions (yes/no), and (4) attended last session for graduation (yes/no). For bivariate tests, Wilcoxon rank-sum test will be used to examine differences in continuous variables between the intervention and control group. The chi-square test will be used for categorical data (Fisher’s exact test will be used when there are small cell counts). In addition, we will conduct exploratory analyses among intervention group participants in a pre/post-intervention analysis. Primary outcomes will be examined using the Wilcoxon signed-ranked test to examine difference among intervention participants from pre-intervention to post-intervention. Furthermore, we will examine whether there is correlation within groups and, if so, will then control for group membership in the analysis.

We will then build exploratory linear (continuous outcomes) or logistic (dichotomous outcomes) regression models to examine the effect of study arm on primary and secondary outcomes, and examine mediating effects of stigma on primary outcomes in mothers and exploratory outcomes in infants. We will prioritize objective measures in examining antenatal and ART outcomes and use self-report measures as a check on these findings. We will examine changes in predictors (e.g., stigma) between time points by creating difference variables and also examine these predictors as time-varying covariates in the regression model using generalized estimating equations (GEE) and structural equation models (SEM). A focus will be to examine whether changes in primary outcomes in mothers from baseline to post-intervention predict changes in primary outcomes at follow-up. If possible, SEM will also be used to examine structural relationships between latent constructs in the conceptual framework (e.g., among stigma subscales) and measured variables. Statistical significance will be assessed as *p* < 0.05. Statistical analysis will be conducted in Stata 16.

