Since 2002, Botswana has provided a transformative national program to offer free antiretroviral therapy (ART) to all its citizens [15]. While eligibility was initially based on CD4 count, since 2016, Botswana has implemented a “Treat All” strategy to offer free ART immediately upon diagnosis of HIV [16]. Botswana is also one of the few sub-Saharan countries to offer free antenatal care for all mothers [17], with > 94% of mothers using antenatal services [14]. Prevention of mother-to-child transmission (PMTCT) of HIV is also a well-established and effective aspect of antenatal care in Botswana [14], where treatment follows the WHO “Option B+” guidelines of lifelong ART use for mothers regardless of CD4 count. Despite the availability of ART, particularly for mothers, challenges exist in maintaining postpartum adherence to ART in Botswana. Postpartum loss-to-follow-up and reduced ART adherence has been identified as a high priority worldwide [18]; a meta-analysis of 51 studies showed that ART adherence declined across countries from 76% prepartum to 53% postpartum [19]. While > 90% of pregnant mothers initiate ART in Botswana [14], results from a recent randomized controlled trial (RCT) suggest a significant drop-off in postpartum adherence [20]. Studies from neighboring South Africa, which like Botswana is a middle-income country that provides free ART [15], also show an increased loss-to-follow-up postpartum [21–23]. Explanations include mothers’ decreased motivation after having protected their neonate from HIV during pregnancy and birth and severe stigma leading to lack of disclosure of HIV [22, 24]. The traditional practice of Botsetsi [25], the semi-compulsory confinement where mother and infant do not leave the home up to 3 months postpartum, may also impact postpartum ART adherence in Botswana. Stigma’s effect on treatment adherence is represented in Fig. 1.

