### Setting

Gaborone is the largest city and capital of Botswana. The catchment area it services has a total population of approximately 270,000 [70, 71], and approximately 2800 Gaborone women give birth each year [72]. Approximately 30% of these women had a positive HIV diagnosis, with about a third already knowing their diagnosis and two thirds testing positive during the current pregnancy (2007–2008 data) [73]. HIV diagnoses for pregnant mothers are often first made through routine PMTCT at sexual reproduction clinics. Newly diagnosed pregnant women are referred to obstetric care at Ministry of Health (MOH) antenatal clinics and often receive HIV care at the Infectious Disease Care Clinic (IDCC) of Princess Marina Hospital for continued ART (including postpartum).

Recruitment takes place at a sub-group of government health clinics offering antenatal services in the Greater Gaborone District Health Management Team (GGDHMT) area and identified by GGDHMT as high-volume facilities. We cluster these clinics geographically such that each cluster (a) typically encounters patients meeting the eligibility criteria at a rate that allows for the formation of a group of 10–12 participants who could be allocated to receive the entire eight-session intervention prior to delivery (anticipated from the 36th week of pregnancy) and (b) has clinics near enough to one another such that participants recruited from any clinic in a cluster would not need to travel far to attend a cluster-wide intervention group session. This allows for the creation of two clusters: Tlokweng (3 clinics) and Gaborone-West (3 clinics).

The following recruitment procedures and eligibility requirements for participants were refined based on feasibility and finalized during piloting of the first intervention group.

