### Eligibility

All pregnant women registering to receive antenatal care at these health clinics who are identified as having HIV and meet the inclusion criteria are eligible to be included in the trial; both primiparous and multiparous women may participate. In addition to being a pregnant woman receiving antenatal care and having HIV, participants are screened at the time of recruitment to ensure they meet the study inclusion criteria of being (a) 18–45 years of age, (b) a Botswana citizen, (c) English or Setswana speaking, and (d) no more than 28 weeks pregnant at the time of recruitment (to allow sufficient time to participate in the intervention prior to delivery). Women are expected to be in HIV care per national HIV treatment guidelines [16]; however, they are not required to be on ART treatment at the time of enrollment. The study excludes from participation (1) women who experienced a miscarriage prior to 28 weeks and (2) women unavailable to attend weekly 90-min sessions for eight sessions prior to week 36.

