### Condition assignment and blinding

Due to pragmatic challenges of recruiting pregnant women during the first 28 weeks of pregnancy, we are not able to use randomization. Participants who meet eligibility criteria are assigned by the research team to receive MME or TAU based on timing of recruitment (Fig. 2). Since we are not able to standardize the start of the intervention to the same week of pregnancy for participants, women are enrolled as long as it is feasible for them to complete eight sessions prior to week 36 of their pregnancy. In terms of blinding, participants and study staff administering the intervention are aware of treatment allocation; lead and senior investigators are blinded to treatment allocation. The biostatistician is not involved in the intervention assignment and is unblinded at the phase of analysis because the intervention group has measures immediately post-intervention that are not administered to the control group. Additionally, one of the primary analyses is to compare outcomes in the intervention group vs. the control group.

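### Three of the four dose cut-points depend partly on when a woman delivers, so they are biased towards an apparent MME benefit on preterm birth and birthweight

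*Protocol article*

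**What the plan says.** The Statistical analysis section makes intent-to-treat the comparison between arms. The outcomes it names include "secondary outcomes for infants including birthweight, timing of delivery, and developmental milestone". Shortly afterwards it adds: "Sensitivity analyses will be conducted based on the dose of intervention received using several different cut-points". The four cut-points are any session attended, the number of sessions, five or more sessions, and "4) attended last session for graduation (yes/no". The sentence restricts none of them to particular outcomes.

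The timing of sessions is set elsewhere in the article:

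- **Setting:** groups are formed so that women can "receive the entire eight-session intervention prior to delivery (anticipated from the 36th week of pregnancy").
- **Eligibility:** a woman may be "no more than 28 weeks pregnant at the time of recruitment".
- **Condition assignment and blinding:** the starting week is not standardised, and "women are enrolled as long as it is feasible for them to complete eight sessions prior to week 36 of their pregnancy".
- **Recruitment:** sessions are at least weekly and may be twice weekly on request, so that more women can finish before they give birth.
- **Introduction:** describes a custom of "semi-compulsory confinement where mother and infant do not leave the home up to 3 months postpartum".

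Antenatal adherence, measured as the number of antenatal visits, is a primary outcome (Primary outcomes; Treatment adherence). The infant outcomes are exploratory, and the study is not powered for them (Secondary outcomes).

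**The concern.** Attendance is treated as the exposure, and gestational age at delivery (with birthweight, which follows it) as the outcome. Yet delivery can end attendance. To be counted at the last session, a woman must normally still be pregnant on that date, so preterm births before that date fall into the low-attendance category by construction. This is reverse causation of the immortal-time kind. It affects the session count and the five-session cut as well as graduation.

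What is at stake is a misleading supportive result. A dose gradient on preterm birth or birthweight could be read as backing for MME. The Discussion says that promising child outcomes should lead to powered studies, so a spurious gradient could distort that planning. The number of antenatal visits is probably affected in the same direction, because an early birth shortens the time for both sessions and visits.

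**Working it through.** The article gives no figure on this point, so there is none to reproduce. The check asks what these contrasts show when MME has no effect.

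**When the last session can fall.** Eight weekly sessions span 7 weeks from first to last. A woman who starts at 28 weeks would have her last session at about 28 + 7 = 35 weeks, inside the limit of week 36. Eight twice-weekly sessions span about 3.5 weeks, so the same woman would finish at about 31.5 weeks. Women recruited earlier can finish earlier still. The exposure to this bias therefore varies widely between groups.

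**Simple model.** All inputs are assumptions, because the article gives none of them:

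- r = 0.20, the proportion delivering preterm.
- f = the share of preterm births that occur before the group's last session.
- 80% of women still pregnant attend the last session; none attend after delivery.

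Preterm among graduates = r(1 − f) / (1 − rf).

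Preterm among non-graduates = [rf + 0.2·r(1 − f)] / [rf + 0.2(1 − rf)].

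| f | Graduates | Non-graduates |
|---|---|---|
| 5% | 0.19/0.99 = 19.2% | 0.048/0.208 = 23.1% |
| 10% | 0.18/0.98 = 18.4% | 0.056/0.216 = 25.9% |
| 30% | 0.14/0.94 = 14.9% | 0.088/0.248 = 35.5% |
| 50% | 0.10/0.90 = 11.1% | 0.12/0.28 = 42.9% |

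If graduates were instead compared with TAU, the TAU figure under no effect would be 20% in every row.

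**Simulation with other assumptions.** There were 400,000 women per scenario and no MME effect. Preterm risk was 10% to 25%, and preterm births fell on average 2.5 weeks before week 37. Attendance was 75% per session while pregnant and nil afterwards. Birthweight rose 170 g per week of gestation, with SD 400 g. The last session fell in one of four windows between weeks 28 and 36.

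- Between 5% and 54% of preterm births came before the last session, depending on the window.
- Graduates had fewer preterm births and heavier babies in all 16 scenarios. The birthweight gap ran from +38 g to +356 g.
- At 15% preterm risk, graduates v non-graduates were 14.4% v 16.8% (last session at weeks 28–31), 13.6% v 19.0% (weeks 30–33), 9.8% v 27.0% (weeks 33–36) and 7.3% v 30.8% (weeks 35–36).
- For the five-session cut at 15% risk and weeks 33–36, preterm was 12.3% v 30.4%.
- The cut at one or more sessions was almost unaffected: 14.8% preterm in that group against 14.8% overall.

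**Chance of a significant result.** The power section's example has 15 intervention women. In the simple model with f = 50%, only 15 × 0.20 × 0.5 = 1.5 of them would be misplaced. Simulated Fisher's exact tests of graduates against non-graduates gave p < 0.05 in roughly 14–15% of trials with 15 MME women and 40–42% with 30. At f = 30% the figures were roughly 6–7% and 18–19%.

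The effect on antenatal visits was not calculated.

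**The case against.** The strongest reply concerns scope. The dose sentence names no outcome, and it does not say whether the contrast is within MME or against TAU. Coverage of the infant outcomes is inferred from unrestricted wording placed just after those outcomes are named. A condensed article may also leave such restrictions to a fuller document. The inference stands as the natural reading, but it is an inference. What can be criticised is that the article fixes specific cut-points that do not suit outcomes it lists.

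Second, the dose analyses are labelled as sensitivity analyses and the infant outcomes as exploratory. This is true, and it limits the harm. A reader might infer that the trial's main comparison is compromised. The article does not support that: the intent-to-treat comparison keeps every woman whatever her attendance.

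Third, the size may be small. Week 28 is the latest recruitment and week 36 the latest finish, and twice-weekly sessions are allowed; the Discussion says such requests have been met. At f = 5% the contrast is only 19% v 23%. This also stands, so the large contrasts describe groups that finish late.

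Fourth, a reader might infer that a false dose-response is bound to be reported. At about 15 MME women it is not, as the test simulation shows; the final sample size is not given.

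Finally, the confinement custom is cited in the article for postpartum ART adherence, not for session attendance. It makes a return to sessions unlikely but does not prove it. The bias needs only that delivery lowers attendance.

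**Conclusion.** The concern holds for three of the four cut-points (session count, five or more sessions, graduation) when they are applied to timing of delivery and birthweight. The direction follows from the article's own schedule, provided that women who have delivered attend less. The size rests wholly on assumed figures and runs from slight to large, mainly according to how late the group finishes. Number of antenatal visits is probably biased the same way, by an unknown amount; this matters because antenatal adherence is a primary outcome.

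The consequence is a possibly misleading supportive result, mostly on exploratory outcomes. It is not a wrong main result. Nor does it condemn every dose analysis: the cut at one or more sessions is nearly free of this bias. The article should correct the point, but it is not critical to the trial's conclusions.

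**What to change.** Add one sentence to the Statistical analysis section. For birthweight, gestational age or preterm delivery, and number of antenatal visits, either omit the second, third and fourth cut-points or use them only in a landmark analysis. The landmark set would be MME women still pregnant on the date of their group's scheduled last session. Any comparison with TAU would be limited to TAU women still pregnant at the same gestational age. The cut at one or more sessions and the intent-to-treat comparison stay as planned.

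The cost is small. Attendance, infant date of birth and gestational age are already collected, and group start and expected end dates are set when sessions are scheduled. The downside is that births before the landmark leave the dose analysis, though they remain in the intent-to-treat analysis. The landmark removes only this bias: attendance is still self-selected, so any remaining gradient should be read with that in mind.
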